## Abstract

**Background:**

Stroke is the leading cause of acquired disability in France. While 90% of patients recover the ability to walk, it is often limited with a steady speed of approximately 0.7 m/s. This limitation of walking activity is partly related to a decrease in strength associated with more or less significant spasticity. In particular, it seems that the strength of the dorsiflexor muscles is directly related to walking speed. We hypothesise that a protocol based on gestural repetition targeted at the ankle during the subacute phase potentiates the recovery of motor control, improving walking activity, and participates in recovering better social participation.

**Methods:**

An estimated total of 60 patients with subacute stroke will be recruited to participate in this multicentre, interventional, prospective, randomised controlled trial.

All participants will benefit from conventional rehabilitation. In addition, the experimental group will take part in an ankle isokinetic rehabilitation programme for 6 weeks (at least 25 sessions). The control group will receive the same duration of conventional rehabilitation.

The primary outcome measure will be a 10-m walking speed at post-intervention. Secondary outcomes will include social participation, walking spatio-temporal parameters, and dorsiflexor strength. Outcome measurements will be taken at baseline, immediately after treatment (6 weeks), then at 6 months and 1 year of follow-up.

**Discussion:**

This study aims to provide scientific evidence that a protocol based on an early over-solicitation of the ankle dorsiflexor muscles to promote their “awakening” can serve to achieve a more effective walking activity, which in turn encourages social participation following discharge from the hospital.

This protocol should also help optimise physical medicine and rehabilitation practices: the more systematic use of the isokinetic dynamometer as a technique associated with, and integrated into the conventional rehabilitation protocol would allow an objective evaluation of the rehabilitation benefits and should increase the rehabilitation gain in central nervous system disorders.

**Trial registration:**

Limoges University Hospital is the sponsor of this research (Unique Protocol ID: 87RI18_0010)

This research is supported by the French Ministry of Health (PHRC 2020-A03328-31) and is conducted with the support of DGOS (PHRC interregional – GIRCI SOHO).

The study protocol was approved by the French Human Subjects Protection Review Board (Comité de Protection des Personnes Nord-Ouest III) on February 23, 2021.

The trial was registered in the ClinicalTrials.gov registry (NCT04800601) on March 16, 2021.

## Administrative information

Note: the numbers in curly brackets in this protocol refer to SPIRIT checklist item numbers. The order of the items has been modified to group similar items (see http://www.equator-network.org/reporting-guidelines/spirit-2013-statement-defining-standard-protocol-items-for-clinical-trials/).

Role of sponsor {5c}	The sponsor has taken the initiative for a clinical trial and assumes the responsibilities and funding for this latter. In practice, the sponsor is responsible for the entire organisation, implementation and monitoring of the clinical trial: choosing the investigator, ensuring data management and carrying out quality controls, obtaining the favourable opinion of the human subjects’ protection review board and the authorisation of the competent authority, taking out insurance and declaring to the competent authority any undesirable events that occur during the research.

## Introduction

### Background and rationale {6a}

Stroke management is a real public health issue in view of the frequency, the mortality rate and the risk of disability for victims. The main post-stroke disability is hemiplegia. When it affects the lower limbs, it often results in a loss of muscle strength associated with varying degrees of spasticity. Walking activity is then impacted. Kwong et al. [1] and Faria-Fortini et al. [2] define walking activity as the best predictor and the most related to social participation. Thus, if it is not fully recovered, the individual's reintegration into society can be problematic, leading to a decrease in quality of life and social participation.

In a recent systematic review, Mentiplay et al. [3] confirmed that muscle weakness is a major contributor to decreased motor performance, in particular walking speed. Specifically, this review shows that the strength of the dorsal ankle flexor muscles is most strongly correlated with walking activity compared to other lower limb muscle groups. Kwong et al. [1], in a more recent study, confirmed these findings. They showed that, more than the other muscle groups assessed (plantar flexor muscles, knee flexor and extensor muscles), dorsiflexion strength is clearly related to walking activity. Most studies, however, have focused on strengthening knee or hip muscles. Only a few studies (randomised controlled) have studied the effects of ankle-specific management on walking activity (May et al. [4], Hsieh [5], Park et al. [6], Yoo et al. [7], An and Won [8], Rydwik et al. [9]). With the exception of the May et al. study, patients in these studies had a long post-stroke delay (8 to 62 months).

It is well known that, given the central origin of motor impairment, neuroplasticity mechanisms play a central role in stroke recovery [10]. Gestural repetitions can enhance this mechanism. Thus, task-oriented therapies such as treadmill exercises can improve gait velocity after a stroke [11]. As slow velocities and abnormal gait patterns often persist, however, Forrester et al. [12] suggest a need for additional strategies to improve walking.

According to the Cochrane review by Pollock et al. [13], motor rehabilitation should be started early and practiced with sessions of 30 to 60 min, 5 to 7 days a week.

In this context, we hypothesise that a protocol based on gestural repetition targeted on the ankle during the subacute phase, potentiates the recovery of motor control, improving walking activity, and participates in recovering better social participation.

### Objectives {7}

The primary objective is to evaluate the impact of an analytical and repetitive ankle mobilisation programme (combined with conventional rehabilitation including repetitive gait training) on comfortable walking speed over 10 m at the end of the intervention.

The secondary objectives are (1) to evaluate the impact of the programme on social participation at 6 months and 1 year, and to measure its evolution, (2) to evaluate the impact of the programme on the spatiotemporal parameters of walking at the end of the intervention and to measure their evolution at 6 months and 1 year, (3) to evaluate the impact of the programme on the progression of walking speed at 6 months and 1 year, (4) to evaluate the impact of the programme on dorsiflexor muscle strength and to measure its progression over time, at baseline and just after the intervention, along with at 6 months and 1 year of follow-up, (5) to evaluate the impact of the programme on the use of technical aids and on the number of falls between 6 months and 1 year, and (6) to evaluate the relationship between dorsiflexor muscle strength, walking speed and social participation.

### Trial design {8}

We plan an experimental, multicentre, parallel-group, randomised, controlled trial (1:1): control group vs. experimental group.

## Methods: Participants, interventions and outcomes

### Study setting {9}

The RCT (Randomised Controlled Trial) will be conducted at five centres (physical medicine and rehabilitation departments of Bordeaux, Limoges, Marseille, Poitiers and Bidard). Participants will be recruited from each respective inpatient stroke rehabilitation unit over a period of eighteen months.

### Eligibility criteria {10}

The study is presented to all patients hospitalised in the physical medicine and rehabilitation departments for a first stroke and meeting all other eligibility criteria: (1) they are within 15 days to 3 months of stroke onset (ischaemic or haemorrhagic); (2) they have persistent foot lift deficiency (Medical Research Council testing: MRC<5); (3) they are able to walk alone at least 10 m with or without technical assistance; (4) they do not have pain in the paretic lower limb (AVS<2); and (5) they are cleared to participate in physical therapy.

Patients will be excluded from the study if they (1) have cognitive or phasic disorders preventing them from understanding the instructions: Boston Scale BDAE<2; (2) had gait disorder before the stroke; (3) have fixed contracture of the ankle (irreducible equinus); (4) are too spastic: Modified Ashworth (MAS) greater than or equal to 4; (5) are pregnant, have a desire for pregnancy or are breastfeeding; and (6) are under curatorship or guardianship or under the protection of justice.

### Who will take informed consent? {26a}

The investigator will inform the patient. Patients will be enrolled after providing written informed consent. The informed consent is signed by the patient and the investigator.

### Additional consent provisions for collection and use of participant data and biological specimens {26b}

If a patient withdraws consent, their data will be removed from the database and not used for analyses. In the event of study discontinuation, the data may be retained if authorised by the patient. In such cases, primary and secondary outcomes will be evaluated at the date of discontinuation.

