**Fig. 1 Fig1:**
[figure not shown]
Schedule of enrolment, intervention, assessment and follow-up

The *primary outcome* is defined as walking speed measured over 10 m at the end of the intervention (6 weeks).

The *secondary outcome* includes social participation evaluated at 6 months and 1 year, walking spatiotemporal parameters measured at each visit, walking speed measured at 6 months and 1 year, along with dorsiflexor strength evaluated at each visit.

The use of technical aids to walk and the number of falls will be described.

Finally, correlations between walking speed/dorsiflexor muscle strength and walking speed/social participation will be studied.

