#### Randomisation

Eligible patients who agree to participate will be asked to give their written informed consent, and will then be randomised into the EG or CG. We will randomise the patients at the first clinical examination. The randomisation process will be ensured using a secure internet connection with access by individual user ID and password and encrypted data transmission to the randomisation platform of the Clinical Research Unit of the Limoges University Hospital. Only the study methodologist will complete and keep the randomisation list on a secure server. In the event of a computer problem, a paper randomisation list will be available. This randomisation list will not include a stratification factor. All actions carried out on this platform, along with the identity of the person who made the changes, will be automatically archived by audit trail procedure. As soon as a patient is randomised, an email will automatically be sent to all study organisers, i.e. the clinical research assistant, data manager and principal investigator. No strategy is provided for preventing a potential imbalance between intervention and control group allocation.

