### Sample size {14}

We calculated the number of subjects in reference to the study by Gharib et Rabab, 2017 [23]. The average speed is 0.58+/−0.09 m/s in the control group and 0.67+/−0.11 m/s in the experimental group. The estimated difference between the 2 groups is 0.09 m/s. For a first species risk of 0.05 and a power of 90%, bilaterally, the number of subjects required is 54 subjects (27 per group) plus 10% (to compensate for those lost to follow-up or excluded from study). The number of patients to be included is therefore 60 (30 subjects per group).

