#### Primary endpoint analysis

The comparison of the mean walking speed over 10 m measured at the end of the intervention (week 6) will be done by a Student’s *t* test if the variable follows a normal distribution (Shapiro-Wilks test) or by a non-parametric Mann-Whitney test otherwise.

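### Outcomes of patients who discontinue are evaluated at the discontinuation date, which conflicts with the week-6 primary endpoint and the fixed secondary visits

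*Protocol article*

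**What the plan says.** Section {26b} of the protocol article separates two ways of leaving.

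- Withdrawal of consent: "If a patient withdraws consent, their data will be removed from the database and not used for analyses".
- Study discontinuation: "In the event of study discontinuation, the data may be retained if authorised by the patient". The next sentence sets the timing of the outcomes: "In such cases, primary and secondary outcomes will be evaluated at the date of discontinuation".

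Elsewhere the timing is fixed by visit. Under Outcomes {12}, the primary outcome "is defined as walking speed measured over 10 m at the end of the intervention (6 weeks"). The section Primary endpoint analysis repeats this: "The comparison of the mean walking speed over 10 m measured at the end of the intervention (week 6) will be done by" a t test or a Mann-Whitney test, with no covariate. Social participation (SIPSO) is due at 6 months and 1 year. Gait parameters and dorsiflexor strength are due at every visit.

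Consent comes before allocation: "Eligible patients who agree to participate will be asked to give their written informed consent, and will then be randomised into the EG or CG". Anyone who leaves after that is a randomised patient, and section {17a} says that patients know their arm. The sample size section adds 10% "to compensate for those lost to follow-up or excluded from study". Section {20c} provides for describing missing values, replacing them if relevant, and testing robustness with extreme scenarios.

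**The concern.** Patients enter 15 days to 3 months after stroke, and the trial's rationale is that walking recovers during this phase. A speed taken at week 2 or 3 is therefore expected to be lower than the same patient's week-6 speed. If it is entered as the primary outcome, the week-6 comparison contains values from other weeks. Because the field is filled, nothing in {20c} is triggered: the value is neither counted as missing, nor replaced, nor varied in the robustness analysis.

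Two effects can follow. If early exit is equally common in both arms, the difference is diluted, because early leavers have had only part of the programme. If it is more common in one arm, that arm's mean is pulled down. The effect is understated when the excess is in the experimental arm and overstated when it is in the control arm. In an open-label trial, the decision to leave can depend on the arm.

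The same rule unsettles the secondary outcomes. Erasure on withdrawal raises a smaller, related question: randomised patients disappear from the comparison, and the article does not say that they will be counted by arm.

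**Working it through.** **1. The rule set against the schedule**, for a patient who leaves at week 3 and allows data to be kept:

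| Outcome | Time fixed in the plan | Time under {26b} |
|---|---|---|
| 10-m walking speed (primary) | Week 6 | Week 3 |
| Gait parameters, dorsiflexor strength | Each visit | Week 3 |
| SIPSO | 6 months and 1 year, analysed as the 12-month minus 6-month difference | Week 3; the difference is undefined, or zero if the one value fills both places |

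The article does not say how the third column relates to the second.

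**2. The plan's own sample size.** Inputs from Sample size {14}: means 0.58 and 0.67 m/s, SDs 0.09 and 0.11, two-sided alpha 0.05, power 90%.

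- Pooled SD = √((0.09² + 0.11²)/2) = √0.0101 = 0.1005
- n per arm = 2 × (1.960 + 1.282)² × 0.0101 / 0.09² = 26.2, rounded up to 27, so 54 in total
- With 10% for losses: 54 / 0.90 = 60

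The stated 54 and 60 are reproduced.

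**3. Bias if early exit differs by arm.** Bias = x × g × m, where x is the excess share of early leavers in one arm, g the walking-speed recovery over six weeks, and m the fraction of it missed at exit. The documents give none of the three, so all are assumptions; m is set at 0.5 (exit halfway).

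- Low: 0.05 × 0.1 × 0.5 = 0.0025 m/s (3% of 0.09)
- Middle: 0.10 × 0.2 × 0.5 = 0.010 m/s (11%)
- High: 0.10 × 0.3 × 0.5 = 0.015 m/s (17%)

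If nearly all recovery is missed (m = 1, exit just after baseline), these figures double. For scale, the standard error of the difference with 30 per arm is 0.1005 × √(2/30) = 0.026 m/s, so 0.010 is about 0.4 standard errors.

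**4. Dilution if early exit is equal.** Diluted difference = 0.09 × (1 − e(1 − f)), where e is the share measured early and f the fraction of the treatment effect already present. Both are assumptions. Power is from the two-sided noncentral t, with the SD held at 0.1005.

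| Patients per arm | e | f | Difference (m/s) | Power |
|---|---|---|---|---|
| 30 | 0 | – | 0.090 | 92.7% |
| 30 | 10% | 0.5 | 0.0855 | 90.0% |
| 30 | 10% | 0 | 0.081 | 86.6% |
| 27 | 0 | – | 0.090 | 89.8% |
| 27 | 10% | 0.5 | 0.0855 | 86.6% |
| 27 | 10% | 0 | 0.081 | 82.8% |

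Rows two and three use the whole 10% allowance on early values. Row four uses it on lost patients. The last two rows lose 10% and measure a further 10% early, which goes beyond the allowance.

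**5. Erasure.** The 10% allowance covers the lost numbers (row four). It does not address selective loss. If 10% of one arm is erased and those patients average one SD below the arm's mean (assumed), the mean of the rest rises by 0.10 × 1 × 0.1005 / 0.90 = 0.011 m/s.

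**The case against.** The strongest reply is that {26b} describes only an exit assessment. It does not say that the exit value enters the primary test, two other sections hold that test to week 6, and the full protocol or SAP, not shown here, may settle the matter. This stands in part: substitution is the plain reading but not the only one. Still, the sentence calls the exit measurement the primary and secondary outcomes, and nothing in the article limits its use. The harmless reading also needs a clarifying sentence.

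A second reply is that the size is assumed and small. This stands. An excess of 10 percentage points is 3 of 30 patients, half the whole-trial allowance of 6, all in one arm and all before week 6. The first two visits take place during hospitalisation, so much of the loss may come later and leave the primary outcome untouched.

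A third reply is that erasure after withdrawal is a consent and ethics decision, and that {26b} already lets discontinuing patients authorise retention. This stands as well, which is why erasure is only a secondary point.

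A reader might infer more than the text supports:

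- **That safety data are lost.** The article removes data from the database, but serious adverse events are reported separately to the sponsor, and nothing says those reports are erased.
- **That {20c} cannot help with erased patients.** Extreme-scenario replacement needs only the number missing per arm, and the randomisation platform's audit trail could supply it. Such scenarios bound the bias without removing it.
- **That stopping the sessions counts as leaving.** The section speaks of study discontinuation and does not equate the two.

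**Conclusion.** The conflict is on the page: one section times the outcomes by the date of leaving, the others by scheduled visit. Taken literally, the first puts early speeds into a week-6 comparison in a way that the missing-data provisions would not detect. The likely effect is modest: about 0.0025 to 0.015 m/s of bias against a 0.09 m/s target if exit differs by arm. If exit is equal and uses the full 10% allowance, power is 86.6% to 90.0%, against 89.8% if those patients were simply lost. These figures rest on assumed exit rates, recovery and timing. Only exits before week 6 affect the primary outcome; later exits affect the 6-month and 1-year outcomes in the same way. The documents do not support a claim that the trial's result would be invalid. They do support replacing the rule, because the repair is cheap and removes an avoidable source of bias.

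**What to change.** Replace the last sentence of {26b} with a rule to this effect:

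1. The week-6, 6-month and 1-year assessments are still sought on their scheduled dates from patients who discontinue and agree to be assessed.
2. A measurement taken at exit is stored with its actual date. It may inform imputation or a mixed model but is not used as the week-6, 6-month or 1-year value.
3. A scheduled value that is not obtained is missing and is handled under {20c}.

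As a secondary change, ask patients who withdraw consent whether data already collected may be kept, as {26b} already does for discontinuation. Report the number erased by arm so that the {20c} scenarios can include them.

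The visits are already planned: week 6 during hospitalisation, the later ones within usual follow-up. The cost is an amendment to the withdrawal wording, which may need the ethics committee's opinion under {25}. Trial status shows recruitment in progress, so the new wording would apply mainly to patients who consent after it.

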### Interventions

#### Explanation for the choice of comparators {6b}

We wish to compare a new rehabilitation technique to conventional rehabilitation. The control group is therefore the one with conventional treatment (the two groups have the same treatment duration).

#### Intervention description {11a}

All patients will receive conventional physiotherapy rehabilitation for 1 h per day, 5 days a week. This conventional management will be performed at the same location, under the guidance of the same physical therapist team to ensure consistent performance of the protocol and safety of all enrolled patients. Conventional rehabilitation includes repeated active and/or passive mobilisations, stretching and postures to inhibit associated spasticity, neurofacilitation techniques, sensory-motor rehabilitation. As soon as possible, patients will be put on their feet, upright with work on balance and weight transfer associated with walking training, repetitive, with technical assistance if necessary. Finally, a fall prevention programme will be implemented. Both groups receive the same amount of rehabilitation.Experimental group (EG): the experimental procedure will consist of analytical retraining of the ankle on an isokinetic dynamometer to awaken motor control and promote strength gain. It will consist of an additional 30 min of isokinetic ankle rehabilitation. The patient is installed on the seat of the isokinetic dynamometer. The trunk-thigh (hip) angle is set at 85°, the thigh-leg (knee) angle at 50° and the foot-leg (ankle) angle at 90°. In order to stabilise the position, the trunk, thigh and foot of the tested leg are strapped. The joint range for plantar flexion/dorsiflexion movement is determined for each subject, subjectively based on how each individual feels. The dynamometer performs automatic gravity correction.

Analytical ankle retraining consists in performing a series of plantar flexion/dorsiflexion movements in CPM (Continuous Passive Mobilisation) mode. The instruction given to the patient will be to accompany the movement by pressing (plantar flexion) or pulling (dorsiflexion) with their foot as hard and as fast as possible, with the intention of achieving maximum active movement. In this way, patients without control are in passive mobilisation but with the intention of achieving voluntary movement. Patients with low motor skills are in assisted active movement and patients with sufficient control are in concentric contraction. The CPM training modality allows subjects to work regardless of the level of recovery in order to reactivate analytical motor control of the ankle.

Among the protocols already published with stroke patients in the acute phase, Vér et al. [14] proposed 210 passive movements in the acute phase in 30 min, 5 times per week. With chronic patients, Forrester et al. [12] proposed 720 active movements in 1 h 3 times per week. The duration of the protocols is most often 5 (An et Won [8], An et Jo [15]) to 6 weeks (Forrester et al. [12, 16]).

From these data, we propose a re-training of 300 movements in 30 min, 5 times a week for 6 weeks, with a minimum of 25 sessions. The protocol comprises 6 sets of 50 repetitions at 30°/s (2min 45 per set) interspersed with 2 min of rest, i.e. a session lasting a total of 28min 30.2-Control group (CG): the comparative procedure consists of a conventional rehabilitation programme as described before. Patients in CG will have a supplement in conventional rehabilitation equal to the additional time of the experimental group (30min).

